## Abstract

**Background:**

Vaginal laxity is an underreported condition that negatively affects women’s sexual function and their relationships. Evidence-based studies are needed to better understand this complaint and to discuss its treatment options. Thus, we present a study protocol to compare the effect of radiofrequency and pelvic floor muscle training in the treatment of women with complaints of vaginal laxity.

**Methods/Design:**

This is a prospective, parallel-group, two-arm, randomized clinical trial (Registry: RBR-2zdvfp–REBEC). Participants will be randomly assigned to one of the two groups of intervention (Radiofrequency or Pelvic Floor Muscle Training). The study will be performed in the Urogynecology outpatient clinic and in the physiotherapy outpatient clinic at the State University of Campinas–UNICAMP and will include women aged ≥ 18 years and with self-reported complaints of vaginal laxity. Participants will be assessed at baseline (pre-intervention period) and will be followed up in two periods: first follow-up (30 days after intervention) and second follow-up (six months after intervention).

**Expected results:**

The results of this randomized clinical trial will have a positive impact on the participants’ quality of life, as well as add value to the development of treatment options for women with complaints of vaginal laxity.

**Trial registration:**

Registry: RBR-2zdvfp–Registro Brasileiro de Ensaios Clínicos–REBEC (19/02/2020).

## Introduction

Vaginal laxity (VL) is defined by the International Urogynecological Association (IUGA) and the International Continence Society (ICS) as a complaint of excessive vaginal flaccidity [1]. This condition is rarely discussed between patients and their doctors, possibly due to the lack of evidence-based treatments, embarrassment and lack of knowledge in the assessment of this condition [2]. According to urogynecologists, VL still presents itself as an underreported condition with reports of discomfort that can affect sexual function and relationships [3, 4]. The way women perceive their genitalia has a strong and positive impact on their sexual function [5].

The prevalence of VL is 24% and appears to be associated with younger age, vaginal births, pelvic organ prolapse (POP) symptoms or physical exam findings. Therefore, it is a somatic, not psychogenic, dysfunction [6].

It is speculated that pregnancy and childbirth play a role in VL [3]. Although there is no proven link between VL and childbirth, research shows that vaginal delivery can result in pelvic floor injury [6, 7]. Pelvic floor and vagina trauma during pregnancy and vaginal delivery can lead to the lengthening of the vaginal opening leading to permanent changes in sexual and physical sensitivity during sexual intercourse. These changes promote an important reduction in the quality of life of women and their partnership [8, 9].

Potential consequences associated with vaginal delivery that extend beyond the postpartum period are urinary incontinence (UI), POP, chronic pelvic pain (CPP), and sexual dysfunction [10–13]. Not all women adapt to the psychological and physical changes in the postpartum period, which can lead to changes in the emotional relationship with their partner [14]. Both vaginal delivery and levator ani muscle trauma are associated with an increase in the diameter of the genital hiatus [15]. The genital hiatus is limited by the puborectalis muscle, a component of the levator ani muscle, and appears to play an important role in defining the high vaginal pressure zone [16]. Avulsion of the levator ani muscle, especially if proven bilaterally, would have some effect on female sexual function [17].

The diagnosis of VL has been based on patients’ self-reporting. A comprehensive medical history, physical examination and psychosexual assessment are the initial steps to properly identify patients with VL [18].

The reduction in vaginal sensation during sexual intercourse may be related to anatomical damage to the perineal body, POP stage 1, laxity of the vaginal canal or introitus, damage to the nerves and connective tissue during pregnancy and childbirth or, potentially, a combination of these factors [19].

Surgical and non-surgical treatments for VL have been proposed. Surgical procedures for VL such as posterior colporrhaphy or perineorrhaphy are more commonly recommended. These procedures aim to reduce the size of the vaginal introitus, not necessarily treating the VL pathophysiology. Besides, 83% of the interviewed urogynecologists reported concerns with a potential risk for post-operative dyspareunia [3]. Post-surgical dyspareunia would further impair the quality of life of a woman who already complained of sexual dysfunction. Thus, it is necessary to develop non-surgical techniques that can assist in the treatment of other factors associated with VL, such as muscle hyperdistensibility and not just surgically reducing the size of the genital hiatus.

A non-surgical option for the treatment of VL includes pelvic floor muscle training (PFMT), which was initially recommended as a first-line treatment for UI [2, 20]. Pelvic floor muscle function appears to play an important role in female sexual function, and contraction of the levator ani muscle appears to increase the sexual response [21]. The contraction of the pelvic floor muscles also plays an important role in the female orgasmic response. Women with weak muscles who receive pelvic floor rehabilitation and strengthen the muscles in that region perceive a positive effect on their sex life [22]. Pelvic floor muscle training could have an effect on the hypertensile muscles of women complaining of VL.

Another non-surgical therapeutic possibility to treat VL is radiofrequency (RF). Despite the scarcity of controlled clinical trials to evaluate the therapeutic advantages, safety and efficacy of radiofrequency [23], the studies carried out to date have shown good tolerance, as well as, subjective improvement of vaginal narrowing, sexual function and decreased sexual discomfort [2] with effects maintained by 12 months and without any adverse events [8]. RF seems to improve vaginal vascularization and collagen fiber reorganization, which may also contribute to a decrease in the sensation of VL [24].

To our knowledge, to date, no clinical trial has been developed to assess the role of pelvic floor muscle and radiofrequency training in VL. Thus, the general objective will be to compare the effect of RF and PFMT in women with VL symptoms. The specific objectives are related to the assessment of the sexual function, vaginal symptoms, and sexual distress, as well as, to assess the impact of UI on patients’ quality of life. The POP staging, contractility, and pelvic floor muscle function will be also evaluated. Finally, we will assess the impression of improvement in VL complaints after the interventions.

Our hypothesis is that RF will be different from PFMT in treating women with VL symptoms.

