### Eligibility criteria

We will include women aged ≥ 18 and ≤ 60 years, with VL complaints assessed by direct question (yes / no) and by the VLQ [2] (very loose, moderately loose, slightly loose), and willing to attend treatments on the scheduled date and places.

Participants who present the following conditions will be excluded from the study: use of a pacemaker; decompensated heart disease; cognitive deficit; peripheral or central neurological disorders; the presence of any type of cancer; the presence of cervical dysplasia; history of active urinary or vaginal infection; decompensated metabolic diseases; patients undergoing physical therapy for pelvic floor disorders; patients using vaginal estrogen in the last 6 months; patients already undergoing surgery for prolapse or urinary or anal incontinence; patients with stage 2 POP onwards; force of contraction of the pelvic floor muscles equal to zero according to the modified Oxford scale [35].

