Pelvic Organ Prolapse Quantification (POP-Q): the ICS recommends POP description and staging using this instrument [48, 49]. The staging classification is defined as [50] Stage 0: there is no demonstrated prolapse; Stage I: the most distal part of the prolapse is more than 1 cm above the level of the hymen; Stage II: the most distal portion of the prolapse is between 1 cm above the hymen and 1 cm below the hymen; Stage III: the most distal portion of the prolapse is more than 1 cm beyond the plane of the hymen, but everted at least 2 cm less than the total vaginal length; Stage IV: complete eversion or eversion of up to 2 cm from the total length of the lower genital tract. The hymen is the reference point used to describe the quantitative prolapse and represents the zero point. Six anatomical points will be evaluated with the aid of a disposable graduated ruler. Two on the anterior vaginal wall (Aa and Ba). Two on the posterior vaginal wall (Ap and Bp) and two points on the upper vagina (C and D). The genital hiatus, the total vaginal length and the perineal body will also be measured. All points will be measured in Valsalva maximum, except the total vaginal length [50]. The ICS clinically defined significant POP in stage II or higher [49, 50].

Pelvic Floor Muscle Strength (PFMS): the strength of the pelvic floor muscles will be graduated according to the modified Oxford scale (5-point) by means of bi-digital vaginal palpation with the patients in the supine position with the lower limbs supported [35].

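### POP stage is to be evaluated as an outcome, but eligibility leaves only one possible improvement, from stage I to stage 0; the centimetre POP-Q values should carry the comparison

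*Protocol article*

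**What the plan says.** The Introduction of the protocol article lists, among the specific objectives, "The POP staging, contractility, and pelvic floor muscle function will be also evaluated". Under Secondary outcomes, POP-Q is introduced with the words "the ICS recommends POP description and staging using this instrument", followed by definitions of stages 0 to IV. The two lowest are "Stage 0: there is no demonstrated prolapse" and "Stage I: the most distal part of the prolapse is more than 1 cm above the level of the hymen". The same paragraph adds "The ICS clinically defined significant POP in stage II or higher".

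Eligibility criteria exclude "patients with stage 2 POP onwards".

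The POP-Q outcome is more than the stage. The protocol also says "Six anatomical points will be evaluated with the aid of a disposable graduated ruler" (Aa, Ba, Ap, Bp, C and D) and "The genital hiatus, the total vaginal length and the perineal body will also be measured". The section on follow-up assessment repeats the physical examination at 30 days and at six months. Data analysis gives general rules: chi-square or Fisher's exact test for categorical variables, and analysis of variance or rank tests for numerical ones. It does not say which form of POP-Q carries the between-arm comparison, and the rules include no baseline adjustment.

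**The concern.** The objective names stage as the quantity to evaluate, while the eligibility rule removes every stage from II upwards at entry. A five-level scale therefore starts with two levels. One of them cannot improve, and the other can improve by a single step. By the protocol's own definition, no participant has clinically significant prolapse at baseline.

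If stage is compared between arms under the general categorical rule, the result may be null because few women were able to improve, and not because the treatments do the same thing to the anatomy. A reader could then take it as evidence of no anatomical effect. More informative measurements come from the same examination, so this risk can be avoided at no cost.

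**Working it through.** **Plan's own figure.** There is none for POP-Q. The total of 68 (34 per arm) rests on FSFI changes of 7 and 3 points, so it neither supports nor contradicts anything here.

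**Step 1: what stage can do.** From the eligibility criteria and the stage definitions:

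| Stage at entry | Can improve to | Can worsen to |
|---|---|---|
| 0 | none | I or higher |
| I | 0 only | II or higher |
| II to IV | excluded at entry | excluded at entry |

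**Step 2: how much this limits a comparison of improvement.** Let s be the share of women at stage I at entry and r the share of those who move to stage 0. The proportion improving in an arm is p = s × r, which cannot exceed s. Neither s nor r is in the document, so both are assumed: r = 10% in one arm and 50% in the other, with s varied. Arm sizes are n = 34 as planned and, after the stated 30% loss, 34 × 0.7 = 23.8, about 24.

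Normal approximation, two-sided alpha 0.05: power = Φ[(|p1 − p2| − 1.96 × SE0) / SE1], where SE0 = √[p̄(1 − p̄) × 2/n] and SE1 = √{[p1(1 − p1) + p2(1 − p2)]/n}.

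Example with s = 50% and n = 34: p1 = 0.05, p2 = 0.25, p̄ = 0.15. SE0 = √(0.1275 × 2/34) = 0.0866 and SE1 = √(0.235/34) = 0.0831. Then (0.20 − 0.1697)/0.0831 = 0.364, and Φ(0.364) = 0.64.

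| Share at stage I (s) | Improving, arm against arm | Power, 34 per arm | Power, 24 per arm |
|---|---|---|---|
| 10% | 1% vs 5% | 0.16 | 0.12 |
| 25% | 2.5% vs 12.5% | 0.34 | 0.26 |
| 50% | 5% vs 25% | 0.64 | 0.49 |
| 100% | 10% vs 50% | 0.97 | 0.88 |

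The approximation is generous where counts are small. Summing the binomial probabilities of all pairs of counts for which Fisher's test gives p ≤ 0.05, at 34 per arm, yields 0.005, 0.128, 0.528 and 0.945 for the four rows. The pattern is the same: the limit is severe if few women are at stage I and mild if nearly all are.

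**Step 3: the centimetre measurements.** For a numerical variable, the difference detectable with 80% power is (1.960 + 0.842) × √(2/n) SD:

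- 34 per arm: 2.802 × √(2/34) = 0.68 SD
- 24 per arm: 2.802 × √(2/24) = 0.81 SD

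These figures are not on the same scale as the powers in Step 2, because no common treatment effect links them. They show only that a length in centimetres is not held to two levels by the stage exclusion.

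**The case against.** The best reply is that the listed secondary outcome is the POP-Q examination, not the stage alone. The ruler points and the three lengths are recorded at every visit, the general rules already give numerical variables a numerical test, and no passage says that the between-arm comparison will be on stage. The choice of POP-Q variable is often left to an analysis plan, which is not shown. The stage 0 versus I distinction also has a stated rationale: the Introduction names stage 1 prolapse among possible contributors to reduced vaginal sensation. Anatomy is further covered by the separate ultrasound outcomes.

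Most of this stands, and it limits the point. A reader might infer that the POP-Q outcome as a whole has almost no room to improve; the centimetre measurements show otherwise. A reader might also infer that a stage comparison will be null whatever the treatments do. That does not follow either, as the table above shows for a high stage I share. A further illustration cuts a normal measurement at the 0/I boundary, assuming a shift of 0.8 SD and a stage I share of 30%, 50% or 70%. Fisher's test on the split then has about 48%, 64% or 65% power at 34 per arm, against about 88% for Mann-Whitney on the measurement. This shows the general cost of dichotomising. It does not model the exclusion or the stage 0 floor, and it cannot single out the genital hiatus, since stage as defined does not use it.

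What the reply does not remove is that the objective names stage, that eligibility leaves stage one step of possible improvement, and that nothing in the text says the measurements take precedence.

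**Conclusion.** The point holds for improvement in stage. Every woman enters at stage 0 or I, so the only improvement available is I to 0. This follows from the document's text without any assumption. Its practical size depends on the share of women at stage I, which the document does not give; under the assumed 10% against 50% regression, power at 34 per arm runs from 0.16 to 0.97 by the normal approximation. Stage can still worsen, and the POP-Q measurements are not restricted to two levels.

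One component of one secondary outcome is affected. The primary outcome (the Global Response Assessment) and the sample size are not. The change is worth making because it is nearly free and guards against misreading a coarse comparison.

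**What to change.** In the Introduction (objectives), Secondary outcomes and Data analysis:

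- State that the between-arm POP-Q comparison uses the centimetre measurements already collected, adjusted for the baseline value. Genital hiatus, Ba, Bp and C are examples; the investigators should choose the variables and fix their order in advance.
- Report stage descriptively by arm and visit, with the number of women in each arm who progress to stage II or higher.
- State that a null comparison of stage will not be read as absence of an anatomical effect.

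The cost is wording only: no added visit, measurement or participant. The article says the trial is still recruiting, so the change can precede the analysis. The one small drawback is that results appear in centimetres and not in the more familiar stages.

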## Materials and methods

### Trial design

This is a prospective, parallel-group, two-arm, randomized clinical trial. It involves three assessments in which primary and secondary outcomes will be evaluated: one pre-intervention visit, one 30-day post-intervention visit, and a six-month consultation after the intervention. Participants will be randomly assigned to one of the two groups of intervention (RF or PFMT). The study will follow the CONSORT recommendations [25] and the SPIRIT Statement (Standard Protocol Items: Recommendations for Interventional Trials) [26]. Fig 1 shows the detailed study steps.

**Fig 1 pone.0259650.g001:**
[figure not shown]
Description of the study steps. F1: Follow-up (30 days after intervention); F2: Follow-up (6-months after intervention); w: week; PFMT: Pelvic Floor Muscle Training; BMI: Body Mass Index; ICIQ-VS: International Consultation on Incontinence Questionnaire—Vaginal Symptoms; ICIQ-SF: International Consultation on Incontinence Questionnaire Short-Form.

The term VL was recently defined and little is known about this complaint. There is still no gold standard treatment for VL and further studies are needed to understand its pathophysiology. Although its pathophysiology is not completely known, there is a consensus on the association of VL with pregnancy and childbirth [2, 10, 27]. Some proposed mechanisms involve overstretching of the vaginal walls and introitus during vaginal birth and an increase in levator ani hiatal dimensions resulting from macro and microtrauma of the levator ani muscle [7, 17]. Although supervised PFMT is recommended as a first-line treatment for stress or mixed UI in women by most of the guidelines [28–30], more studies are needed to demonstrate the effect of PFMT on female sexual function. A randomized controlled trial concluded that women reporting improvement in sexual function demonstrated greatest increase in PFM strength and endurance [31].

Regarding RF, a recent randomized, multicenter, sham-controlled clinical trial found a statistically significant and clinically important improvement of VL with RF when compared with Sham treatment [32]. In our study, RF will be applied once every 4 weeks (a total of three applications) and will probably be less likely to face problems related to treatment adherence when compared to PFMT. Although the RF procedure has been shown to be well tolerated, adverse effects may occur [32, 33]. PFMT is generally free of adverse effects.

### Study setting

Patient recruitment and assessment/treatment will be carried out in the Urogynecology outpatient clinic at the School of Medical Sciences and in the Physiotherapy outpatient clinic at the Centro de Atenção Integral à Saúde da Mulher (CAISM)—Hospital da Mulher [name]. José Aristodemo Pinotti, both units affiliated to the State University of Campinas—UNICAMP.

### Study population

Women with self-reported complaints of VL. There is no objective and standardized diagnostic evaluation for VL and its pathophysiological mechanism is not yet known [34].

### Sample size

The sample calculation was based on the study by Krychman *et al*. [32], who demonstrated that RF therapy was associated with significant clinical and statistically significant improvement in sexual function in women with VL, when data analysis was performed in a group containing 73 patients. To calculate the sample of the present study, we used values of sexual function assessed using the FSFI questionnaire. There was an increase of 7 points in the FSFI score in the group treated with radiofrequency and an increase of 3 points in the control group. When considering a study power of 80%, an alpha of 0.05 with two-tailed test, it was found that the minimum number of participants required in each group will be added to a percentage of 30% loss in the sample, totaling 68 women, 34 in each group (isolated RF and isolated PFMT).

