### Primary outcomes

The primary outcome will be the indication of improvement in the VL symptoms after the proposed interventions assessed through a single question with seven possible answers. The Global Response Assessment (GRA) [2] is a 7-level scale with response to the question: “How are you now (levels of vaginal laxity/tightness and sexual satisfaction) compared to before treatment” (markedly improved, moderately improved, slightly improved, no change, slightly worse, moderately worse, markedly worse?). This scale item has been already used to evaluate improvement in vaginal laxity symptoms after treatment [2].

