### Secondary outcomes

The description of secondary outcomes is described below together with their measurement instruments.

Female Sexual Function Index (FSFI) [39]: a brief and multidimensional instrument to assess sexual function in women. The questionnaire was developed and validated by Rosen *et al*. and consists of 19 items that investigate sexual response over the past four weeks and performance in six domains: sexual desire, arousal, lubrication, orgasm, satisfaction, and pain [39]. The validation in Portuguese took place in 2008 by Thiel *et al*. [40]. The answers are scored according to the sum of the items that make up each domain (simple score) and multiplied by the domain factor generating the weighted score [40]. The maximum score is 36 points, adding up the total of each domain. Wiegel *et al*. proposed a cut-off score to differentiate women with or without sexual dysfunction in the amount of 26.55 [41].

Female Sexual Distress Scale-Revised (FSDS-R): a self-report questionnaire with 13 questions scored on a 5-point Likert scale from 0 (never) to 4 (always) to assess the sexual distress. Sexual distress is characterized by a set of feelings (for example, unhappiness, guilt, frustration, stress, worry) and emotions that individuals have about their sexuality. It differs from sexual dysfunction related to symptoms of sexual function, such as arousal, orgasm and pain, separate from emotions [42]. The Portuguese translation was developed by Berenguer *et al*. [43].

International Consultation on Incontinence Questionnaire—Vaginal Symptoms (ICIQ-VS): is a 14-item questionnaire validated for the Portuguese language by Tamanini *et al*. that assesses the presence and the impact of vaginal symptoms, as well as their relationship with quality of life [44, 45].

International Consultation on Incontinence Questionnaire Short-Form (ICIQ-SF): validated in Portuguese by Tamanini *et al*., is a simple, brief, and self-administered questionnaire, capable of quickly and effectively assessing the impact of urinary incontinence on patients’ quality of life. It consists of four questions that assess the frequency, severity, and impact of urinary incontinence. Your score can vary from 0 to 21, the greater the commitment, the higher the total value [46, 47].

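### The stated 80% power belongs to FSFI, a secondary outcome, and to a radiofrequency-versus-sham difference; it does not describe the primary GRA comparison with active pelvic floor training

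*Protocol article*

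**What the plan says.** The Sample size section of the protocol article states: "To calculate the sample of the present study, we used values of sexual function assessed using the FSFI questionnaire". It takes a 7-point rise with radiofrequency (RF) and "an increase of 3 points in the control group" from a cited RF trial (reference 32), with 80% power and two-sided alpha 0.05. On the loss allowance it reads: "the minimum number of participants required in each group will be added to a percentage of 30% loss in the sample, totaling 68 women". This makes 34 per group. It gives no SD, no evaluable number before the loss allowance, and no assumption about GRA.

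Under Primary outcomes: "The primary outcome will be the indication of improvement in the VL symptoms after the proposed interventions". The instrument is one item: "The Global Response Assessment (GRA) [2] is a 7-level scale with response to the question". FSFI is the first instrument listed under Secondary outcomes: "Female Sexual Function Index (FSFI) [39]: a brief and multidimensional instrument to assess sexual function in women".

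The text after Figure 1 describes reference 32 as a sham-controlled trial that found "improvement of VL with RF when compared with Sham treatment". The present trial has no sham arm. The Introduction states the hypothesis as a difference between RF and PFMT.

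**The concern.** The power statement is separated from the primary comparison in two ways.

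- **Outcome.** It is computed for a continuous secondary score, while the primary outcome is a single ordinal item. Power for one says nothing about power for the other without further assumptions, and none are given.
- **Contrast.** The 3-point control change comes from a sham arm. Assigning it to PFMT assumes that PFMT does no better than sham on FSFI. The article does not justify this, and its Introduction gives a rationale for some benefit of PFMT on sexual function.

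A reader will take 80% as the chance of detecting a worthwhile difference in the main analysis. The Discussion anticipates what would follow if the two therapies proved equally effective. If a non-significant GRA result were read that way, the 80% figure would lend it support that it cannot give. Per protocol is the primary population in Data analysis, so the number left after losses and discontinuations is the one that counts.

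**Working it through.** **Inputs from the article.** FSFI difference 7 − 3 = 4; two-sided alpha 0.05; power 80%; loss 30%; 34 per arm; 1:1 allocation. **Not given:** SD of FSFI change, evaluable n per arm, GRA rates or distribution, expected PFMT effect. Values used for these are assumptions.

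**1. Can 34 per arm be reproduced?** Not from the stated inputs, because n per arm ≈ 2(1.960 + 0.842)² SD² / 4² = 0.981 SD², and the SD is missing. Working back from 34:

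- Loss added: 26 × 1.3 = 33.8, which rounds to 34.
- Loss divided out: 24 / 0.7 = 34.3, which rounds to 34. An unrounded n between 23.1 and 23.8, divided by 0.7 and rounded up, also gives 34. On the total, 47 / 0.7 = 67.1, rounded up to 68.

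Solving the two-sample t-test for 80% power:

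- n = 24: standardised difference 0.826, so SD = 4 / 0.826 = 4.84.
- n = 26: standardised difference 0.792, so SD = 4 / 0.792 = 5.05.

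**2. FSFI power if PFMT does better than sham.** Two-sample t-test, 24 evaluable per arm (0.7 × 34 = 23.8):

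| True gap | SD 4.84 | SD 5.05 |
|---|---|---|
| 4 points | 80% | 77% |
| 3 points | 56% | 52% |
| 2 points | 29% | 27% |

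The 3- and 2-point gaps are illustrations; the article gives no size for a PFMT effect.

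**3. GRA.** The article sets no responder cut. Assume a responder/non-responder split and compute exact power of the Pearson chi-square test:

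| Assumed rates | 24 per arm | 34 per arm (no loss) |
|---|---|---|
| 30% v 50% | 31% | 40% |
| 40% v 60% | 31% | 36% |
| 50% v 70% | 31% | 40% |
| 60% v 80% | 33% | 46% |

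The normal approximation, power = Φ{[|p₁ − p₂|√n − 1.96√(2p̄(1 − p̄))] / √(p₁(1 − p₁) + p₂(1 − p₂))}, gives 28% to 32% at n = 24. For 40% v 60%: (0.2 × 4.899 − 1.96 × 0.707) / 0.693 = −0.586, so 28%.

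By the same approximation, 80% power with 24 per arm needs a difference of 39.5, 38.8 or 36.7 points when the lower rate is 30%, 40% or 50%, and 33.4 points when it is 60%.

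**4. If the loss was added.** With a base of 26 (SD 5.05) and a real 30% loss, power at 23.8 per arm is 76%. With a base of about 24 it stays at about 80%.

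**The case against.** The Sample size section says openly that FSFI was used, so nothing is concealed. Sizing on a validated score with published data, when the primary item has little, is a common compromise. A condensed article may also leave the SD to a fuller document. All of this is fair, but it does not make 80% the power of the GRA comparison, and the article presents it as the study's power without qualification.

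The illustrative figures rest on choices made for this review. The SD is back-solved, the GRA rates and the two-way split are assumed, and an ordinal analysis of all seven levels would give different figures. This limits the precision of the figures but does not affect the mismatch.

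Three stronger readings are tempting, and the documents do not support them.

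- *That the 30% loss was wrongly added rather than divided out.* The article's wording and 26 × 1.3 point that way, but division from about 24 reaches 34 as well. Without the SD or the evaluable n, the text cannot settle it.
- *That FSFI power is below 80% at the planned loss.* This follows only if the loss was added.
- *That the article says PFMT improves sexual function.* The Introduction says only that it could act on the muscles of women with this complaint and reports perceived benefit in women with weak muscles. The text after Figure 1 says that more studies are needed. What stands is that a sham-arm change was borrowed for PFMT without justification.

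**Conclusion.** The point holds on the article's own text. The 80% power and the 68 women come from a secondary outcome and a sham contrast, while the trial's primary question is GRA under RF versus PFMT. No power is stated for that question.

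The possible size is material. If the back-solved SD is about right and PFMT narrows the FSFI gap to 3 or 2 points, power falls to roughly one half or under one third. On a dichotomised GRA with lower-arm rates of 30% to 50%, only a difference of roughly 37 to 40 points would be detected with 80% power at 24 per arm. Even with no losses, a 20-point difference has at most 46% power in the cases examined. These are conditional illustrations, not estimates of the trial's actual power.

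The loss allowance remains a question to the sponsor. At most it moves FSFI power from 80% to about 76%.

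**What to change.** Rewrite the Sample size paragraph and keep 34 per arm:

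1. Say that the 80% applies only to a 4-point FSFI difference taken from a sham comparison, and that FSFI is secondary.
2. State the SD and the evaluable number per arm.
3. State the GRA effect that this number can detect with 80% power, naming the assumed rates or distribution.
4. Add that a non-significant result will not be read as equal effectiveness, and bring the Discussion into line.
5. Say whether the 30% was added or divided out. If it was added to a base of 26, correct the power at a real 30% loss to about 76%; otherwise leave it.

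The cost is one rewritten paragraph, one sentence in the Discussion and a less favourable power statement. No extra participants are needed. Recruitment is under way, so the change should be made before any outcome data are analysed.
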